### Objectives

The main objective of the POXIPEN trial is to assess the efficacy of IVO vs placebo on maximal bladder capacity in children with neurogenic bladder secondary to myelomeningocele (spina bifida), performing intermittent catheterisation, and for whom oral anticholinergic therapy has been deemed ineffective or associated with adverse effects.

Secondary objectives are:
To assess evolution of maximum bladder pressure after IVO (or placebo);To assess incontinence (i.e., time to clinical failure of treatment as perceived by the patient) after IVO (or placebo);To describe treatment tolerance and adverse effects;To assess the number of responders and continent patients after IVO (or placebo);To assess usability of IVO;To assess changes in patients’ quality of life after IVO (or placebo);To describe changes in patients’ voiding diary data after IVO (or placebo);To describe changes in urodynamic and in renal ultrasound parameters after IVO (or placebo);To identify patients’ characteristics associated with a greater likelihood of responding to IVO.

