### Sample Size

Schröder et al. [11] found a 32% increase in maximum bladder capacity in adults using IVO compared with baseline values (*P* < 0.001). In our target population, Raes et al. [29] found a 33% increase in maximum bladder capacity when treated with tolterodine. As patients included in our study already use catheterisation, there is no reason to expect a strong placebo effect from instillation. Given the lack of precise data on the effect of IVO in our target population and based on experts’ opinion, we expect a 33% increase in maximum bladder capacity in the treated group, a 5% increase in the placebo group, a mean (SD) initial bladder capacity of 170 (80) mL, and a correlation between measurements for the same patient of 0.8. To obtain a power of 0.9 with a type I error risk set at 0.05, 26 patients per group are needed. To allow for a margin of error, we rounded up the total expected sample size to 60.

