### Statistical Analyses

For the primary outcome, an intention‐to‐treat analysis will be conducted to assess the difference between the two groups in the evolution of maximum bladder capacity, using a linear mixed model accounting for repeated measurement, age stratification, and treatment exposure as a binary variable. A secondary exploratory analysis will be conducted to account for any imbalance that may occur between groups despite randomisation due to the small sample size. Multivariate linear regression will be performed, adjusted for age and gender.

Given the small sample size and the short duration of follow‐up for each patient, there should be little or no missing data. For the primary outcome, patients lost to follow‐up will be assigned the value measured during the last cystomanometry performed (i.e., last observation carried forward).

No intermediate analysis is planned given the small sample size.

Two secondary outcomes will be analysed following a fixed sequence in a priori ordered hypotheses:
Maximum bladder pressure after 4 weeks of treatment: the two groups will be compared using the same methodology as for the primary outcome;Time to treatment failure: the two groups will be compared using a two‐tailed log‐rank test. If a patient is lost to follow‐up, the date of treatment failure will be the date of last news plus 1 day.

Occurrence of AEs will be compared in the two groups using a Fisher's test with a significance threshold = 0.05.

The proportions of responders and continent patients after 4 weeks of treatment will be calculated with their 95% CI.

Standardised differences in patients’ quality of life assessed with the KIDSCREEN‐10 and ICIQ‐UI‐SF questionnaires will be compared between the two groups using a Wilcoxon test, with a significance threshold = 0.05. As recommended by the KIDSCREEN‐10 developers, an additional subgroup analysis will be performed to distinguish children aged 6–7 years from those aged 8–17 years.

Changes in voiding diary elements, urodynamic parameters, and renal ultrasound parameters after 4 weeks of treatment will be compared using a Wilcoxon test, with a significance threshold = 0.05.

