Product usability will be assessed using the linear transformation of the UMUX‐LITE score proposed by the authors and comparing the average scores in both groups to reference scores (e.g., a score >80 is associated with good usability). A median score will be calculated in the two groups for the supplementary usability questions specific to our study.

Finally, the association between responder status and the following variables will be tested using a Fisher's test, with a significance level = 0.05:
Cause of discontinuation of oral anticholinergic treatment (inability to swallow, no effect on bladder hyperactivity, intolerable side effects);Neurological status (walking vs non‐walking, presence of a ventriculoperitoneal shunt valve);Concomitant diseases;Concomitant treatment.

All analyses will be conducted with R statistical software, version 4.0.3 (R Foundation for Statistical Computing, Vienna, Austria).

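### Responder and continence rates get no between-arm contrast, and the predictor tests carry no treatment term, so they cannot be read as showing who benefits from IVO

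*Protocol article*

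**What the plan says.** All references are to the protocol article.

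- **Objectives.** One secondary objective is to assess how many patients respond or become continent after IVO or placebo. The last one is to identify patients' "characteristics associated with a greater likelihood of responding to IVO".
- **Endpoints.** A responder has at least a 50% reduction in diary incontinence episodes at 4 weeks and no intolerable adverse event. The definition does not refer to arm, so a child on placebo can be a responder.
- **Statistical Analyses, responders and continence.** "The proportions of responders and continent patients after 4 weeks of treatment will be calculated with their 95% CI". No difference, ratio or test between arms follows.
- **Statistical Analyses, neighbouring outcomes.** Bladder pressure, time to treatment failure, adverse events and quality of life are each said to be compared between the two groups. Diary, urodynamic and ultrasound changes are compared by Wilcoxon test.
- **Statistical Analyses, predictors.** "the association between responder status and the following variables will be tested using a" Fisher's test at 0.05. The variables are cause of discontinuation of oral treatment, neurological status (walking, shunt), concomitant diseases and concomitant treatment. No treatment term, interaction or restriction to one arm is given.

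**The concern.** There are two gaps.

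First, response and continence are randomised outcomes that matter to families, yet the plan stops at the proportions. A reader left with two separate intervals may take their overlap as no evidence of a difference, when the interval for the difference itself excludes zero.

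Second, the predictor objective is about IVO, but the test has no placebo reference. If arms are pooled, placebo and IVO responders are mixed. If only the IVO arm is used, a child who would have improved anyway looks the same as one who improved because of IVO. Either way, a trait that is only prognostic could be published as a marker of who benefits from IVO.

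**Working it through.** **The plan's own figure.** The only sample size calculation is for the primary outcome: "To obtain a power of 0.9 with a type I error risk set at 0.05, 26 patients per group are needed". The Sample Size section bases this on capacity rising by 33% on IVO and by 5% on placebo, a baseline mean of 170 mL with SD 80 mL, and a within-patient correlation of 0.8.
- Difference: (0.33 − 0.05) × 170 = 47.6 mL.
- SD of change: 80 × √(2 × (1 − 0.8)) = 50.6 mL.
- n per group = 2 × (1.960 + 1.282)² × 50.6² / 47.6² = 23.7, so 24 (two-sided 0.05 assumed). The t-distribution version gives 25.

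This agrees with 26 to within two patients, so the sample size is not in dispute. After "we rounded up the total expected sample size to 60", there are 30 per arm. The article gives no power, responder rate or factor prevalence for the analyses discussed here, so every rate below is an assumption.

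**Separate intervals against the difference.** Assume 18/30 responders on IVO and 9/30 on placebo.
- Wilson 95% CIs: 60% (42.3 to 75.4) and 30% (16.7 to 47.9). They overlap.
- Newcombe lower limit: 0.30 − √((0.600 − 0.423)² + (0.479 − 0.300)²) = 0.30 − 0.25 = 0.05.
- Newcombe upper limit: 0.30 + √((0.754 − 0.600)² + (0.300 − 0.167)²) = 0.30 + 0.20 = 0.50.
- The difference is 30 points, 95% CI 5 to 50; Fisher p = 0.037.

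**The predictor test.** Assume a binary factor present in half of each arm, so 15 children per arm-by-factor cell. The probability that Fisher's test gives p ≤ 0.05 is summed exactly over the binomial outcomes.

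| Assumed responder rates (factor present/absent) | IVO effect by level | Pooled arms | IVO arm only |
|---|---|---|---|
| IVO 70/30, placebo 50/10 | 20 and 20 points (prognostic only) | 86% | 43% |
| IVO 65/35, placebo 35/5 | 30 and 30 points (prognostic only) | 60% | 23% |
| IVO 70/50, placebo 30/10 | 40 and 40 points (prognostic only) | 24% | 10% |
| IVO 70/30, placebo 20/20 | 50 and 10 points (true modifier) | 26% | 43% |

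In the first row, the pooled test compares (70 + 50)/2 = 60% with (30 + 10)/2 = 20%. It sees a 40-point gap although the IVO effect does not vary. It flags this factor far more often than the true modifier in the last row. The IVO-only test sees 70% against 30% in both of those rows, so it cannot tell them apart.

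**With the placebo reference.** A simulated Wald test of the difference between the two risk differences flags the prognostic-only factors of the first two rows in about 6% of trials and the true modifier in 47%. Precision is poor. For the first row the standard error is √((0.21 + 0.21 + 0.25 + 0.09)/15) = 0.225, so the 95% interval is about ±44 points.

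**The case against.** The other side has several good points.

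- **Derivable contrast.** The trial is randomised and double-blind. If the proportions are reported by arm, anyone can compute the difference. Misreading overlapping intervals is then the reader's error. This stands: a reader might infer that the responder data cannot attribute response to IVO, and the documents do not support that. The gap lies in the planned analysis, not in the design.
- **Related construct already compared.** Time to treatment failure counts a reduction below 50% or intolerable side effects as failure, and the arms are compared by log-rank in the fixed sequence. This also stands, but that endpoint adds perceived inefficacy and does not cover continence.
- **Descriptive objective.** The objective speaks of association, and response to IVO can mean response among children given IVO. Tests within the IVO arm would answer that. The arms used are not stated, and a condensed article may leave this to the full protocol, so pooling, and with it the 86%, is not established. The IVO-only figure of 43% is a false signal only if the result is presented as benefit from IVO.
- **Multiplicity.** At least five tests at 0.05 suggest 1 − 0.95⁵ = 23% false claims. That overstates the risk, because Fisher's test is conservative. Its exact size is about 1.7% at 15 against 15, so five independent tests give about 8%. At 30 against 30 it is at most about 2.7%, giving about 13%.

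**Conclusion.** The point holds as a free improvement to secondary analyses. The article plans no between-arm contrast for responders or continent patients, and its predictor tests have no treatment term and no stated arm. A positive Fisher result therefore cannot be read as predicting benefit from IVO. Under the assumed rates, a factor unrelated to the size of the IVO effect is flagged in 24% to 86% of trials if arms are pooled and in 10% to 43% within the IVO arm. These figures rest on assumed responder rates and a factor present in half of each arm. It does not follow that response cannot be attributed to IVO at all, nor that the tests carry a 23% false-claim rate. The primary analysis and the two fixed-sequence secondary analyses are unaffected.

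**What to change.** 1. **Responders and continent patients.** Report the IVO-placebo risk difference with 95% CI (for example Newcombe or Miettinen-Nurminen), stratified by the randomisation age group, beside the proportion in each arm.
2. **Predictors.** Do not pool arms without a treatment term. For each characteristic, report the IVO-placebo risk difference within each level and the difference between levels with its CI, labelled exploratory and imprecise at 60 children. Stay on the risk-difference scale. With IVO 70%/50% and placebo 30%/10%, the effect is 40 points in both levels, but the treatment odds ratios are (0.7/0.3)/(0.3/0.7) = 5.4 and (0.5/0.5)/(0.1/0.9) = 9.0, so a logistic interaction would not be null. Sparse cells also threaten a logistic model: at a 10% rate, 15 children yield no responder with probability 0.9¹⁵ = 21%.
3. **Alternative to 2.** If the Fisher tests are kept, state that they use the IVO arm only and describe the results as association with response on IVO, not as prediction of benefit.

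The cost is a few sentences and a few lines of code, with no new data, visits or patients. The drawback is wide intervals for the between-level differences, which is what 60 children can support.

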### Ethics

Eligible patients and their legal guardians will be informed about the trial objectives, the possibility to have access to and to modify their personal data, and to indicate that they do not want their personal data used for research purpose. This information will be summarised in a written document. In case both parents have parental authority, the inclusion of their child will only be possible if both written consents are obtained. If only one parent is still alive or has parental authority, or when the patient is represented by a legal guardian, only one written consent will be necessary and a copy of the court judgement will be requested for documentation in the patient's file. Minor patients will receive information in a way that is adapted to their ability to understand. They will be informed orally by the investigator and will receive an information letter adapted to their age. Their personal consent for their participation in the study will be sought, and their assent will be documented in the consent form. If the patient reaches the age of majority during his/her participation in the trial, a new information note will be given to him/her, and he/she will have to sign a new consent form at the next visit.

The Comité de protection des personnes (CPP), i.e., French equivalent for the Institutional Review Board, has reviewed the trial protocol under the number 2022‐501902‐36‐00 and approved it. The declaration of compliance with the reference methodology MR001 has been sent to Commission Nationale de l’Informatique et des Libertés (CNIL) on 21 July 2023. The Agence Nationale de Sécurité du Médicament et des produits de santé (ANSM), i.e., the French drug safety agency, has granted authorisation for the trial on 2 January 2025.

## Discussion

### Current Status of the Trial

The trial is funded by a grant from the French Ministry of Health (PHRC‐N‐2021), and FARCO PHARMA laboratories, who will also supply experimental treatment and placebo. The study also received financial support from the Association Nationale Spina Bifida Handicaps (ASBH) and institutional support from the Société Francophone d’Urologie Pédiatrique et de l’Adolescent (SFUPA).

The mandatory French ethic committees granted authorisation for the trial.

The eCRF is achieved. The trial recruitment will be launched in September 2025 and will end on September 2027.

The trial protocol was written according to the Standard Protocol Items: Recommendations for Interventional Trials (SPIRIT) guidelines (Data S5) [30].

### Implications

The POXIPEN trial will be the first RCT to evaluate the efficacy of IVO on neurogenic bladder in children. It should provide a high level of evidence of the benefit of IVO in this patient population. If IVO proves effective in improving maximal bladder volume and pressure, it could lengthen the delay in therapeutic escalation to intravesical onabotulinumtoxinA injection, thereby reducing the risk of complications associated with general anaesthesia in children. Besides, reducing the incidence of bladder leakage could improve patients’ quality of life. For ethical and regulatory reasons, our study population is limited to children aged ≥6 years. If efficacy and safety are demonstrated in this population, future studies should be designed to evaluate IVO in younger children, who represent an important target population. From an individual point of view, if IVO is effective for a patient during the study, it will be possible for the referring investigator to prescribe this treatment as part of a compassionate use after the study. The French regulatory framework could then evolve towards a marketing authorisation by health authorities, thus changing the way paediatric patients with neurogenic bladder disease are managed.

A long‐term evaluation of this treatment, including a medico‐economic evaluation, could be carried out in a second phase, following completion of this study.

## Ethics Statement

This study has been approved by French ethics authorities through the European Union (EU) Clinical Trials Information System (CTIS). The committee's reference number for this approval is EU CT Number: 2022‐501902‐36‐00. Written and informed consent will be obtained from participants’ legal guardians (Data S4) and non‐opposition of minor patients will be sought prior to any study‐related procedures.

## Consent for Publication

Not applicable.

## Data Availability

Data sharing is not applicable to this article as no datasets were generated or analysed during the current study.
